#### Inclusion criteria

Individuals who attend the hospital outpatient clinics due to minor health problems;Whose plasma glucose levels are within the normal range based on the 2006 WHO diagnostic criteria;At the same age group as cases (±3 years); andReside in the same catchment area (metropolitan Hanoi) as the cases.

#### Exclusion criteria

Non-diabetic patients with malignant cancers;Outside the desired age range;Deemed too ill to participate by the medical doctors;In long-term modification of diet due to any reason; andNon-residents, tourists or foreigners.

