Specific objectives of our case–control study are:To determine the association between green tea consumption and risk of T2D.To determine the association between coffee consumption and risk of T2D.To ascertain common foods in the Vietnamese diet (e.g. soy foods, fruits, vegetables, red/processed meat, and white rice-based products) in relation to the T2D risk.To investigate certain macronutrients (e.g. protein, carbohydrate, and fat) and micronutrients (e.g. magnesium, iron, vitamin D, and minerals) in relation to the T2D risk.To determine the association between lifestyle factors (such as smoking, alcohol drinking, and physical activity) and risk of T2D.

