#### Inclusion criteria

Aged 40–65 years;Diagnosed with T2D within 4 weeks before the interview; andBeing able to undertake a 45-min face-to-face interview including measurements.

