#### Exclusion criteria

Deemed too ill to participate by the medical doctors;Diagnosed with T2D more than 4 weeks before the interview;In long-term modification of diet due to any reason; andNon-residents, tourists or foreigners.

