#### Clinical data extraction

Clinical and biochemical laboratory results including fasting plasma glucose, 2 h-OGTT, HbA1c and lipid profile (triglycerides, cholesterol levels) will be extracted from patient log-books on the date of interview. Comorbidities will be inquired by the interviewer and cross-verified against medical records. Family history of diabetes (type 1 or type 2) will be recorded if applicable.

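### Malignant cancer excludes controls but not cases, a small and avoidable source of selection bias, mainly for smoking and alcohol

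*Protocol article*

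**What the plan says.** In the protocol article, the exclusion criteria under Selection of controls begin with "Non-diabetic patients with malignant cancers". The criteria under Selection of cases have no matching item. A case must be in the age range, be "Diagnosed with T2D within 4 weeks before the interview" and be able to complete the interview. A case is excluded if judged too ill, diagnosed too long ago, on a lasting dietary change, or not a resident.

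Three exclusions appear in both lists: "Deemed too ill to participate by the medical doctors" and the two items that read "In long-term modification of diet due to any reason; andNon-residents, tourists or foreigners". The inclusion criteria for controls also restrict the reason for the visit: "Individuals who attend the hospital outpatient clinics due to minor health problems".

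On data, Clinical data extraction states: "Comorbidities will be inquired by the interviewer and cross-verified against medical records". The Discussion raises selection bias in general terms but does not mention the different treatment of cancer.

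**The concern.** Controls should show how common each exposure is in the population that produced the cases. If a condition linked to an exposure removes people from one group only, the two groups no longer come from the same population. Smoking, alcohol and diet are stated objectives of the study, and all may plausibly differ in people with cancer. If smokers are over-represented among people with cancer, removing those people from the controls alone lowers smoking in the controls, and the smoking odds ratio rises for a reason unrelated to diabetes.

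A larger sample does not reduce such a shift. Covariate adjustment in the planned unconditional logistic regression does not handle it properly either. No control can have cancer, so a cancer term has no finite estimate. At best the fit would amount to dropping the cases with cancer, which is better done openly as a restriction.

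**Working it through.** **Side by side**

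| Criterion | Cases | Controls |
|---|---|---|
| Judged too ill | excluded | excluded |
| Lasting dietary change | excluded | excluded |
| Non-resident | excluded | excluded |
| Malignant cancer | no rule | excluded |

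The reason for attendance is already limited to minor problems for controls. The cancer item therefore acts mainly on coexisting cancer, a test that cases do not face.

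**Inputs.** The article gives no figure for cancer or smoking, so all of these are assumptions: cancer share of the source population c = 1%, 2% or 5%; smoking 25% overall; smoking among those with cancer s = 40% or 50%; true odds ratio 1; cancer equally common in cases and source population.

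**Formula.** Under the null, cases smoke at 0.25. Controls without cancer smoke at q = (0.25 − c·s)/(1 − c). The spurious odds ratio is [0.25/0.75] ÷ [q/(1 − q)]. The control odds simplify to (0.25 − c·s)/(0.75 − c + c·s).

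| c | s | Control odds | Spurious OR |
|---|---|---|---|
| 1% | 40% | 0.246/0.744 = 0.3306 | 1.008 |
| 1% | 50% | 0.245/0.745 = 0.3289 | 1.014 |
| 2% | 40% | 0.242/0.738 = 0.3279 | 1.017 |
| 2% | 50% | 0.240/0.740 = 0.3243 | 1.028 |
| 5% | 40% | 0.230/0.720 = 0.3194 | 1.043 |
| 5% | 50% | 0.225/0.725 = 0.3103 | 1.074 |

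**Direction.** If s = 25%, then q = 0.25 and the factor is exactly 1. If s is below 25%, q rises above 0.25 and the factor falls below 1. The sign depends on the exposure.

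**Wider assumptions.** With exposure prevalence of 25–70% and exposure odds 1.5 to 5 times higher in people with cancer, the factor is 1.004–1.020 at a 1% share, 1.007–1.040 at 2% and 1.019–1.103 at 5%.

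**Against sampling error.** With 550 per group and exposure of 25%, the standard error of the log odds ratio is √[2/(550 × 0.25 × 0.75)] = 0.139, so the 95% confidence limits lie a factor of exp(1.96 × 0.139) = 1.31 either side of the estimate. Across prevalences of 25–70% the factor is about 1.27–1.31.

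**Cases affected.** 550 × 1% = 5.5, about 6; 550 × 2% = 11; 550 × 5% = 27.5, about 28.

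**Sample size, for the cost of the fix.** The plan's own figure reproduces. Exposure in cases is 0.66 × 0.70/[1 + 0.70 × (0.66 − 1)] = 0.462/0.762 = 0.606. Against 0.70, with two-sided 5% significance and 90% power, this needs 541–542 per group, depending on the variance form, against the stated 540. Removing 6 or 11 of 550 cases without replacement leaves 544 or 539.

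Applying the cancer rule to both groups, or to neither, returns the factor to 1.00 in this model.

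**The case against.** The strongest reply is that hospital controls may properly be restricted by the diagnosis that brought them to the clinic, and that such a restriction need not bind the cases. If people with cancer are over-represented in the orthopaedic, dental, ENT and gastroenterology clinics, removing them could bring the controls closer to the source population. The article does not settle whether they are. The wording is also open to either reading, clinic diagnosis or any cancer. But the reason for attendance already has its own criterion, and the cancer item is worded as having the disease. Using one rule on both sides removes the difficulty under either reading.

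A reader might infer more than the text supports. One inference is that cases whose diet changed because of cancer stay in. Both lists exclude lasting dietary change for any reason, so this harm is largely answered; only short-term change could remain. Another is that the bias always runs upward. It does not: it reverses for any exposure less common in people with cancer, as current smoking might be if some stop after diagnosis. A third is that the design or the main result is compromised. The figures above assume that every case with cancer stays in, although the shared exclusions remove some, and nothing shows a material effect on green tea, the exposure that sets the sample size.

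The small size is a fair objection and stands. It sets the priority of the point but does not remove the inconsistency. Nor is this a detail lost when the article was condensed, since both lists are printed.

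**Conclusion.** The unequal rule is real and unexplained, and it can bias the odds ratios of cancer-related exposures, chiefly smoking and alcohol. Under the stated assumptions the shift is about 1–3% at a cancer share of 1–2%, and up to 7% at 5%. These are upper values for those inputs, and every input is assumed rather than taken from the article. The shift is far smaller than the 27–31% width of the confidence limits on either side of an estimate. This is a low-severity point, worth correcting because the correction is cheap. It is no ground for doubting the design.

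**What to change.** Add malignant cancer to the case exclusion criteria, and word it identically in both lists so that it covers coexisting cancer whatever the reason for the visit. For cases already enrolled, leave those with cancer out of the main analysis, or at least report a sensitivity analysis without them. The planned comorbidity questions, checked against records, identify them, so no new data are needed.

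The cost is one line of eligibility text, a restriction of the findings to adults without cancer, and the loss of about 6–11 of 550 cases at a 1–2% share. If the rule is applied during recruitment, the lost cases are replaced, because enrolment continues until the target is reached. If it is applied only at analysis, it uses up most or all of the 10-case margin that the plan holds for refusal and withdrawal: at 2%, 539 cases remain against the 540 required, which has a negligible effect on power.

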### Recruitment procedure

On a typical day, the research team members will be present at the hospital outpatient clinics when patient registration begins in the early morning. Eligible T2D patients who agree to participate will be referred by their physicians to the interviewer. The distribution of sex and age of enrolled cases will be continuously updated before the selection and recruitment of controls in the afternoon, who are frequency-matched to cases on sex, age (±3 years), and residential location. After being briefed about the study purpose, each participant will be asked to sign an informed consent form, followed by a face-to-face interview and anthropometric measurements that take on average 45 min to complete. This recruitment process, expected to take 18 months, will continue daily until the desired sample size of n = 1100 is reached.

### Data collection

A structured questionnaire will be administered to each consented participant during the face-to-face interview. This questionnaire comprises several sections related to personal, demographic and residential/contact details, dietary intake, habitual physical activity and lifestyle, followed by clinical information and anthropometric measurements.

#### Dietary assessment

Dietary habits over the three preceding years will be ascertained using a validated semi-quantitative Food Frequency Questionnaire (FFQ), specifically developed for the Vietnamese population (Tran et al. 2013a). This FFQ records the intake of commonly consumed food and beverage items in Vietnam, which are classified into 15 major food groups (soybean products, tomato products, vegetables, fresh fruits, cereal, meat, seafood, egg, cooking oil, seasoning, milk, alcohol, tea, coffee, and juice). The frequency of consumption is documented according to month, week, or day. A portion size (small, standard or large) is estimated via a picture book taken from a previous study (Kusama et al. 2005). Dietary intakes of the 128 food and beverage items, energy and selected nutrients will be computed, with reference to the standard tables of food composition in Vietnam (Khan 2007).

#### Physical activity assessment

Physical activity levels including vigorous and moderate activities as well as walking before the onset of T2D will be assessed by the Vietnamese version of the International Physical Activity Questionnaire-Short Form (Tran et al. 2013b). Sitting time will be inquired about the amount of time spent using computers, watching television, eating meals, reading newspapers/book and sitting on motorbikes, in vehicle or train. Information about sleeping duration will also be solicited.

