### Selection of controls

Controls will be individuals seeking medical care at the outpatient clinics of the departments of orthopaedics, dental, ear, nose and throat, and gastroenterology, who are generally healthy and unlikely to share similar risk profiles as the cases. As a partner of the national diabetes prevention program, all patients attending the hospital outpatient clinics will be screened and tested for T2D by administering fasting glucose test and/or 2 h-OGTT, results of which are entered into the patient log-book and medical record on the day of their visit. The physician will then confirm their diabetes-free status on the basis of the 2006 WHO diagnostic criteria. Eligible controls, being frequency-matched to cases on sex, age (±3 years), and residential location, will be recruited at the same data collection period as the cases. They will be interviewed by the research assistant using the same questionnaire upon their consent to participate in the study.

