There are several strengths of the proposed study, namely, a relatively large sample size to assess different exposures, use of validated instruments for diet and lifestyle assessment, ascertainment of exposure variables via structured interviews, and uniform measurements of clinical and biochemical parameters across case and control groups. Special efforts will be made to increase response rates and minimise withdrawal of participants. However, some limitations warrant attention. Case–control designs are inherently retrospective in nature, as such they are susceptible to biases. For instance, selection bias may arise if only severely ill patients are recruited and the controls are drawn from a different reference population. For this reason, we will select newly diagnosed (incident) T2D patients, while non-diabetic controls are recruited from the outpatient clinics of the same hospital, who are matched to the cases in terms of residential location but are unlikely to share the same risk profiles. Moreover, the hospital serves the entire catchment covering both rural and urban areas of Hanoi, so that our sample of participants should be representative of the underlying adult population. Another potential drawback is recall bias (Armenian 2009), which may lead to spurious associations between exposures and the outcome of interest (Gordis 2000). In this study, a consistent recruitment and interview process is adopted throughout the data collection period and applied to both case and control groups, particularly the use of interviewer-administered questionnaires, which should reduce recall error and bias between the two groups.

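### The physical activity window is tied to T2D onset, which controls do not have and the article does not date in cases, and no common reference date is given

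*Protocol article*

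**What the plan says.** Under Physical activity assessment the article states: "Physical activity levels including vigorous and moderate activities as well as walking before the onset of T2D will be assessed". It gives no length for this period and no matching reference point for people without diabetes. The same paragraph adds sitting time and sleep duration.

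Controls are diabetes-free by design. Selection of controls says: "The physician will then confirm their diabetes-free status on the basis of the 2006 WHO diagnostic criteria". The same section says of them: "They will be interviewed by the research assistant using the same questionnaire upon their consent to participate in the study".

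For cases, the datable event is diagnosis. The inclusion criterion reads: "Diagnosed with T2D within 4 weeks before the interview".

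Diet has its own window, worded once for all participants: "Dietary habits over the three preceding years will be ascertained". The event that these years precede is not named.

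Physical activity is not incidental. One objective is: "To determine the association between lifestyle factors (such as smoking, alcohol drinking, and physical activity) and risk of T2D". Against recall bias, the Discussion offers this safeguard: "a consistent recruitment and interview process is adopted throughout the data collection period and applied to both case and control groups".

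**The concern.** In a case–control study the exposure period has to be definable without reference to the outcome, or be given an explicit counterpart in controls. Here the activity period ends at an event that exists in one group only. In that group it is an event nobody observes, because the article establishes when T2D was diagnosed and not when it began. Each interviewer or respondent would have to supply a reference time for controls, and each case would have to guess at onset.

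At stake is differential misclassification of activity, meaning error in the reported exposure that depends on case status. Such error can create or hide an association, and a larger sample does not reduce it. It also weakens the safeguard that the article itself names, since an interview is not uniform if one of its time frames can be applied to cases only.

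**Working it through.** The point rests on the wording. The arithmetic only shows how sensitive the study would be to an error of this kind.

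1. **The statements side by side.** (a) Activity is to be recalled for the time before T2D onset. (b) Controls have no T2D. (c) Controls answer the same questionnaire as cases. (d) No reference date for controls appears anywhere in the article. If (c) holds, the window in (a) is put to people for whom it has no meaning. If controls are asked something else, (c) and the uniform process claimed in the Discussion do not hold for this item. Either way the three sections do not fit together.

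2. **Cases.** Selection of cases and its criteria establish a diagnosis and a limit of 4 weeks from diagnosis to interview. No onset date is collected or derivable.

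3. **The plan's own figure.** The article gives no figure for this point. Its sample size supplies a benchmark effect. With 70% exposure in controls and an odds ratio of 0.66, exposure in cases is 0.66 × 0.70 / (0.30 + 0.66 × 0.70) = 0.462 / 0.762 = 0.606. The usual two-proportion formula, two-sided 5% and 90% power, gives 541 per group against the stated 540, so the figure reproduces. A common reference date does not change it.

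4. **Sensitivity, continuous activity score.** The shifts are assumptions and are not in the documents. Suppose no true association, equal SDs, and reports shifted by δ SD in cases only. With 550 per group, SE = √(2/550) = 0.0603. The spurious odds ratio per SD is exp(δ), and P(significant) = Φ(δ/SE − 1.96) + Φ(−δ/SE − 1.96).
   - δ = 0.1: exp(0.1) = 1.11; δ/SE = 1.66; P = 38%.
   - δ = 0.2: exp(0.2) = 1.22; δ/SE = 3.32; P = 91%.
   - A shift the other way gives the inverse odds ratios and the same probabilities.

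5. **Sensitivity, binary activity.** Assume 50% truly active in both groups (true odds ratio 1) and a fraction m of active cases reporting as inactive. The observed odds ratio is 0.5(1 − m) / (1 − 0.5(1 − m)), because the control odds are 1.
   - m = 5%: 0.475/0.525 = 0.90.
   - m = 10%: 0.45/0.55 = 0.82.
   - m = 20%: 0.40/0.60 = 0.67, about the size of the 0.66 on which the study is planned.

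6. **Diet.** If the three years end at the interview, the part after diagnosis is at most 28 days out of 3 × 365.25 = 1,095.75 days, or 2.6%. This applies only to a case interviewed at the 4-week limit.

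**The case against.** - **The article is condensed and the questionnaire is not shown.** The questionnaire may well give controls a date, and leaving that detail out of an article would be no fault. This stands as far as it goes. But the article is not silent: it prints a window, and that window does not fit half the sample.
- **The clause has a good purpose.** Asking about the time before disease keeps changes made because of the disease out of the exposure, so it is meant to reduce reverse causation in cases. That is right, and the purpose should be kept. The difficulty is that onset is neither datable in cases nor defined in controls.
- **A reader might infer that controls are asked about current activity, so that the two groups are measured over different periods.** The documents do not say so. The Abstract and Data collection sections speak of habitual activity for participants generally, and controls receive the same questionnaire. The control window is undefined; it is not stated to differ.
- **A reader might extend the point to diet and conclude that its window also differs by case status.** It does not: one wording covers everyone. Anchoring it at the interview is the natural reading but still an inference. The possible post-diagnosis share is small, and the 4-week limit keeps it small. Both groups also exclude people "In long-term modification of diet due to any reason", although the length is not defined and a change made in the last few weeks is not clearly covered. Recall influenced by a recent diagnosis is the ordinary recall bias that the Discussion already acknowledges.
- **The shifts and misreporting rates have no source in the documents.** This is correct. They are no evidence that the wording produces a bias of any given size.

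**Conclusion.** The point holds for physical activity. The printed window depends on the outcome, has no meaning for controls, marks an unobserved time in cases, and conflicts with the same-questionnaire and consistent-process statements elsewhere in the article. It should be corrected because it affects a named exposure and the correction is nearly free.

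The size and direction of any bias are unknown. The figures of 38% and 91%, and the odds ratios of 0.90 to 0.67, follow correctly from assumed errors. They show that modest case-only errors would matter with 550 per group, and nothing more.

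For diet only a secondary point remains: the anchor of the three years is not named, and at most 2.6% of the period could follow diagnosis. The conclusion assumes that the questionnaire does not already set a common date. If it does, the article's wording needs only to be brought into line with it.

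**What to change.** Replace the reference to onset with one stated recall period, identical in both groups and ending on a common index date. For cases this is the date of the diagnostic glucose test. For controls it is the date of the screening glucose test, which Selection of controls says is entered in the log-book on the day of the visit. Apply the same period to activity, sitting and sleep.

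As a secondary change, state that the three years of the diet questionnaire end on the same index date, which removes the up to 28 days after diagnosis in cases.

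Record the index date. Together with the interview date it gives the gap between the two, which may be longer in cases than in controls and can then be described. The index date marks diagnosis and not onset, so behaviour changed by undiagnosed disease would remain a limitation to state.

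The cost is revised interviewer wording and one date field. No visits are added and the sample size does not change.
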